### Procedure for unblinding if needed {17b}

The design is open label so unblinding will not occur.

## Data collection and management

### Plans for assessment and collection of outcomes {18a}

#### Primary outcome—Table 2

We will measure medication adherence using the *eCap electronic pill container*: the most objective and valid method of assessing adherence [31] and a Self-Reported Adherence measures described below. eCap will record the number of times the pill bottle is opened daily, over the course of the study. As in other trials, patients will be given eCap to assess adherence to their most frequently taken CVD prevention medication (e.g., BP or cholesterol-lowering medication) [32], as identified by the primary care physician (PCP). Any medications taken during emergency room visits or hospitalizations will be obtained from patient reports and chart abstraction of patient medical records to avoid erroneously penalizing patients when the eCap is not used. Such days will be removed from the denominator of the formula to compute adherence rates. *Self-reported adherence* will be assessed using *Adherence to Refills and Medications Scale (ARMS)* a 14-item scale with two subscales for taking medications as prescribed and refilling medications on schedule [34, 35].

*Secondary outcomes*—baseline, 6 and 12 mo. (a) Diabetes-specific 5-year CVD risk as measured with UK Prospective Diabetes Study (UKPDS) Engine score, (b) provider engagement as measured by CollaboRATE Shared-Decision Making measure, and (c) patient activation measures (PAM).

We will measure HbA1c using a portable Afinion AS 100 finger stick sample analyzer, which is accurate and has a coefficient of variation <5% as required by the National Diabetes Data Group [49].

#### Measurements

Cholesterol measurements will be obtained from patient charts at baseline, 6 months, and 12 months. Providers will order this test during patients’ visits. We will assess smoking status using a CDC questionnaire [50]. *Blood pressure* (BP) will be measured by the RA at baseline, 6 months, and 12 months for all enrolled patients using a validated automated device (*BpTru*), following AHA guidelines [51]. Three BP measurements will be obtained at 1-min intervals. Average systolic BP (*SBP*) and diastolic BP (*DBP*) will be recorded. Inadequate BP control will be defined as mean SBP > 130 mm/Hg or DBP > 80mm/Hg per 2019 guidelines for DM patients [52].

#### Surveys (Table 2)

Completed at 0, 6, and 12 months: (a) CollaboRATE Shared-Decision Making measure: CollaboRATE, a fast and frugal patient-reported measure of SDM process, contains 3 brief questions that patients complete following a clinical encounter [53, 54] and has inter-rater reliability of .86 at .001 significance. (b) Patient Activation Measure: The Patient Activation Measure (PAM) consists of 13 items that form a scale with a Cronbach’s alpha of .9 [55]. (c) Combined Outcome Measure for Risk Communication And Treatment Decision Making Effectiveness (COMRADE) [56] measures patient satisfaction with physician communication, and patient confidence in decisions made. This scale has good internal consistency (Cronbach’s alpha=.92); (d) Stanford Self-Efficacy Scale for Managing Chronic Diseases – 6-Item Scale with internal consistency of reliability of .91 [57]. (e) Summary of Diabetes Self-Care Activities (SDSCA) Measure, a multidimensional measure of DM self-management; with good internal and test-retest reliability [58]. (f) the Rapid Estimate of Adult Literacy in Medicine (REALM) [59], a widely used measure of health literacy [60] tailored to poor medication adherence [61].

#### Participant characteristics and potential confounders

A comprehensive list of participant characteristics will be collected, including socio-demographic characteristics (including sex, gender, age, etc.), medical history, comorbidities, and health behaviors. System Usability Survey (SUS) [62] used in our Office-GAP study and Way2Health Pilot study will ask about texting, computer, Internet use, and comfort when using a mobile phone and its features. Medications: medication names and their doses will be obtained. We will determine change in proportion of patients on aspirin, other antiplatelet medications, beta-blockers, cholesterol-lowering agents, and angiotensin converting enzyme inhibitors/angiotensin receptor blockers (ACEIs/ARBs). We will collect data on smoking cessation counseling and reduction in proportion of patients’ smoking.

### Plans to promote participant retention and complete follow-up {18b}

#### Retention plan

To maximize retention and prevent attrition, 0–1-, 3-, 6-, 9-, and 12-month follow-up assessments will be scheduled at the preceding visit (Fig. 2); follow-up reminders will occur via text messaging, calls, and mailings beginning 3 weeks prior to each visit. Patients will be compensated $20, $20, $20, $20, and $20 for attending group visit and the 0–1-, 3-, 6-, 9-, and 12-month follow-up visits respectively in the form of gift card, to cover transportation, parking, and time. At the 12-month visit, the control group (texting only) will be compensated $50 while the intervention group (Office-GAP + Texting) will receive $100 in the form of a gift card. Participants that complete an exit interview will receive an additional $40. Using these strategies in our Office-GAP studies with this population had >80% retention rate.

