#### Criteria for discontinuing or modifying allocated interventions {11b}

We try to keep modifications and discontinuation to a minimum in this pragmatic trial. However, if a patient does not consent or withdraws consent from a component of the study, or if a caregiver takes over administration of medications, these may be conditions for disenrollment. Our pragmatic trial takes every opportunity to document any barriers to implementation such as interruptions in cell phone service, scheduled hospitalizations, family vacations, etc., without disenrolling.

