### Confidentiality {27}

The procedures for obtaining research material for the study include anthropometric and BP measurements, laboratory data (e.g., glycosylated hemoglobin {HbA1c}), medical records, interviews, and self-completed questionnaires. Research Assistants (RAs) that are trained and certified will obtain all data according to detailed study protocols. Data will be collected directly from enrolled study participants and medical records and used specifically for research purposes. Baseline data will be obtained during group visits only after the patient has signed the informed consent and the HIPAA form. Follow up data will be obtained at 0–1, 3, 6, 9, and 12 months after office visits with their providers. Only individuals officially assigned to the study team or data management team will have access to individually identifiable information about human subjects. This will include the PI, co-investigators, project coordinator, statistician, and research assistants. All individuals will have completed MSU’s IRB human subjects training and will be included on a staff listing of the MSU IRB. Patient survey information, initially collected using paper forms, will be entered into the REDCap database; EMR data will be abstracted using paper forms and later entered into the REDCap database by RAs; eCAP data will be uploaded into eCAP-Provider cloud storage by RAs and then securely downloaded by the BRIC Data Manager to a secure BRIC server.

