### Methods in analysis to handle protocol non-adherence and any statistical methods to handle missing data {20c}

#### Addressing missingness [82]

In linear and nonlinear mixed models, likelihood-based inference using only the non-missing responses is valid under missing at random (MAR). Missing completely at random is likely to be untenable in our context. Techniques such as inverse-probability weighting will be used to accommodate missing data patterns that are neither MCAR nor MAR [83–85], an approach that we used in analyzing longitudinal censored medical costs data [85, 86].

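### The 12-month visit pays intervention patients twice what controls receive, which invites unequal loss of 12-month data, and inverse-probability weighting is wrongly described as handling data that are not missing at random

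*Protocol article*

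**What the plan says.** **Payments.** The Retention plan gives one schedule for both arms: "Patients will be compensated $20, $20, $20, $20, and $20 for attending group visit and the 0–1-, 3-, 6-, 9-, and 12-month follow-up visits". The money is given "in the form of gift card, to cover transportation, parking, and time". The next sentence sets a different amount by arm for the last visit: "the control group (texting only) will be compensated $50 while the intervention group (Office-GAP + Texting) will receive $100". No reason is stated. An exit interview is paid separately, at $40. Past experience is given as one figure, not by arm: "Using these strategies in our Office-GAP studies with this population had >80% retention rate".

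**What happens at 12 months.** Table 1 lists a blood-pressure check, a review of texting, surveys and exit interviews for both groups. The only extra item for group 1 is the decision checklist. Table 2 has a research assistant administer the ARMS adherence survey, and Measurements has a research assistant take blood pressure. For the electronic pill cap, Confidentiality {27} says "eCAP data will be uploaded into eCAP-Provider cloud storage by RAs", without saying when.

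**Missing data.** Addressing missingness names two approaches. The first is likelihood-based inference in mixed models using the observed responses, described as valid under missing at random (MAR). The second reads: "Techniques such as inverse-probability weighting will be used to accommodate missing data patterns that are neither MCAR nor MAR".

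**The concern.** Adherence at 12 months is one of the two primary time-points, and attendance at the visit where much of it is collected is rewarded differently by arm. Patients know their arm and come from a low-income population, so a gift card of twice the value can plausibly change who attends. The imbalance is made by the trial itself and serves no stated purpose.

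Unequal attendance alone does not bias the comparison. Bias arises if the controls who stay away differ in 12-month adherence from those who come, in a way that earlier data do not reveal. For that case the protocol relies on inverse-probability weighting (IPW). Weights estimated from observed data remove bias only if missingness is random given the variables in the weight model. The protocol therefore names a safeguard for precisely the pattern in which it fails, and a reader of the results could be falsely reassured.

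**Working it through.** **1. The plan's own figure.** The only figure that depends on dropout is the recruitment total. With 320 evaluable patients and successive losses of 10%, 4% and 2% (Sample size {14}):

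320 / (0.90 × 0.96 × 0.98) = 320 / 0.84672 = 377.9, rounded up to 378.

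This reproduces. The allowance is one overall figure (58/378 = 15.3%), not split by arm.

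**2. Does burden explain the payment?** The checklist is the only extra group 1 item at 12 months. It is also used at the 0–1, 3, 6 and 9-month visits, for which the $20 list makes no distinction by arm. The exit interview has its own payment. Nothing stated explains the extra $50.

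**3. The payment list.** The visits named in "for attending group visit and the 0–1-, 3-, 6-, 9-, and 12-month follow-up visits respectively" number six: group visit, 0–1, 3, 6, 9 and 12 months. Five amounts are given. The 12-month visit is thus in the $20 list and also has its own amount, and the text does not say whether $50/$100 replaces the $20 or is added to it.

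**4. Completer contrast under assumed retention.** From Sample size {14}, the planned 12-month adherence is 0.65 (group 1) and 0.42 (group 2), a difference of 0.23. Treat p as the proportion adherent, and let adherent and non-adherent patients be retained with probability rA and rN. Then

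observed rate = p·rA / (p·rA + (1 − p)·rN).

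Group 1 is held at 90% for all its patients. Every retention value is an assumption.

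| Control rA / rN | Control retained | Control observed | Difference | Bias |
|---|---|---|---|---|
| 80% / 80% | 80.0% | 0.420 | 0.230 | 0 |
| 85% / 75% | 79.2% | 0.451 | 0.199 | −0.031 |
| 90% / 70% | 78.4% | 0.482 | 0.168 | −0.062 |
| 90% / 60% | 72.6% | 0.521 | 0.129 | −0.101 |
| 75% / 85% | 80.8% | 0.390 | 0.260 | +0.030 |

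For the third row: 0.42 × 0.90 = 0.378 and 0.58 × 0.70 = 0.406, so 0.378/0.784 = 0.482 and 0.650 − 0.482 = 0.168.

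Unequal retention as such (first row) gives no bias. If less adherent controls are lost, the bias is toward no effect. If more adherent controls are lost, it favours the intervention.

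**5. What the planned methods do.** A simulation of 1,000,000 patients used the planned means and the serial correlation of 0.30, with an assumed SD of 0.25 and normal outcomes. Group 1 retention was 90%. The likelihood analysis under MAR was represented by regression on baseline and 6-month adherence within arm, and IPW used weights from the same variables. In the last two rows control retention followed a logistic model with intercept 1.5 and slope 1.5 per SD of the adherence value named. The true difference is 0.230.

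| Control loss depends on | Control retained | Complete cases | MAR likelihood | IPW |
|---|---|---|---|---|
| Arm only | 80% | 0.230 | 0.230 | 0.230 |
| Observed 6-month adherence | 75% | 0.208 | 0.229 | 0.229 |
| Unobserved 12-month adherence | 75% | 0.160 | 0.168 | 0.168 |

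In the first two rows both planned methods recover the truth. In the third, which is the pattern named in "Techniques such as inverse-probability weighting will be used to accommodate missing data patterns that are neither MCAR nor MAR", IPW is off by 0.168 − 0.230 = −0.062 and does no better than the MAR likelihood.

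**The case against.** The strongest reply is that loss caused by payment is loss caused by arm. Arm is observed, and the model contains group and group-by-time terms, so the MAR likelihood analysis already handles it. This stands, as the first two simulation rows show. A reader might infer that the planned analysis cannot repair unequal attendance at all; the documents do not support that. Nor do they show that unequal payment produces loss related to unobserved adherence. They only leave it possible.

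Second, the pill cap records daily throughout the study, and the adherence index is built over the whole period from baseline. As upload timing is not stated, a missed last visit may cost only the most recent segment. This also stands. The link is firmest for 12-month ARMS and for outcomes measured by research assistants, while cholesterol comes from charts.

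Third, a reader might conclude that any group difference is partly an effect of payment. That goes too far. No unequal payment is stated for the 6-month visit, where a primary hypothesis is also tested, and nothing ties a payment for attending the last visit to pill-taking over the preceding year.

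Fourth, the weighting sentence introduces IPW as one example among techniques, and the weights could use variables that are not in the outcome model. IPW can then help, but it still assumes MAR given those variables, so the description remains wrong. Leaving the details of a sensitivity analysis to an analysis plan is normal; misstating what a method assumes is a different matter.

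Two side matters add little. The five-for-six payment list may be an editorial slip. The wording "if a caregiver takes over administration of medications, these may be conditions for disenrollment" is permissive, is not specific to an arm and has no connection with payment.

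**Conclusion.** The point holds in a conditional form. The 2:1 payment at a primary time-point is explicit, unexplained and avoidable, and it invites unequal loss of 12-month data. If that loss is explained by arm or observed history, the planned likelihood analysis deals with it. If it depends on unobserved 12-month adherence, neither planned method corrects it, and the claim made for IPW is wrong as written.

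Size and direction cannot be computed from the documents. The biases shown, from −0.10 to +0.03 against a planned 0.23, rest on assumed retention and are completer contrasts. The −0.06 for the planned methods rests on the assumed retention model, the SD of 0.25 and normal outcomes. They show what could happen and do not estimate what will.

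**What to change.** - **Payment.** Make the 12-month amount equal in both arms for all remaining visits, for example by raising control to $100. With 8 control teams of 22 patients (176), this costs 176 × $50 = $8,800 if every control visit were still to come, and less for those already past; recruiting 378 rather than 17 × 22 = 374 adds slightly. A consent and ethics-board amendment is needed. The drawback is that control payment then changes over calendar time, so the date of change should be recorded and retention reported before and after it. If the difference is to stay, state its reason.
- **Payment list.** Reconcile the five $20 amounts with the six visits, and say whether the 12-month amount replaces or adds to the $20.
- **Reporting.** Report 12-month retention by arm, separately for ARMS, research-assistant measurements and pill-cap data, and state when pill-cap data are uploaded.
- **Missing data.** Describe IPW as valid under MAR given the weight model, and keep the MAR likelihood analysis as the main one. For departures from MAR, add a delta-adjusted (tipping-point) analysis in which missing 12-month adherence is shifted separately in each arm until the conclusion changes. This needs only a short text change and modest programming.

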### Data management {19}

This study is using the Research Electronic Data Capture (REDCap) system for data entry, coding, security, and storage. Data will be entered by using electronic data capture forms, which will be created by the Biomedical Research Informatics Core (BRIC) from paper forms provided by the PI. The BRIC Data Manager will utilize standard quality assessment features within REDCap to monitor ongoing data quality: e.g., missing data for key variables, distribution of variable values, completeness of form data entry, etc. BRIC will design and deploy a programmatic utility to process eCAP data: downloading cloud data, cleaning, analytical structuring, and “number of days adherence” variable derivation. BRIC will maintain secure storage and backup of the downloaded eCAP data.

#### Data quality

The use of REDCap, which may include a Study-specific data dictionary, adaptive logic, and real time validation rules, with assistance from the BRIC informatics team results in a well-planned data collection protocol and quality assurance strategy.

#### Data sharing

The REDCap system also provides a standard export mechanism, which is easily exported to a variety of types of common statistical packages (SPSS, SAS, Stata, R/S-Plus). This allows the Principal Investigator (PI) to generate data that are truly independent of the method of data entry, thus generating usable, collaborative datasets for sharing and outcome analysis.

### Data monitoring plan

The Director of Biomedical Research Informatics Core will oversee and ensure implementation and monitoring of the data management plan and will be responsible for general oversight of BRIC research efforts and safeguards related to the protection of human subjects’ data. He will work closely with the BRIC Data Managers to ensure that the Informatics configuration, testing, and production processes are conducted appropriately to ensure security and confidentiality of data in the Study’s REDCap database. Data will be entered into the REDCap, by the Research Assistants (RAs) and will be independently verified by the Project Manager/another RA.

#### Data security

The REDCap system was designed specifically around HIPAA-Security guidelines. User access to data can be restricted at the form/survey level. In addition, variables may be designated as ‘identifying’, which excludes their inclusion in data exports. The MSU- REDCap server is housed in a facility which satisfies requirements for the storage of HIPPA data. Security staff patrols, RFID key card access, and audio/video monitoring protect the physical location of the server. The server is connected to a private segment of the BRIC network. The segment is protected through a firewall, which routes traffic and provides active intrusion detection and protection. All web-based information transmission is encrypted and uses Secure Hypertext Transfer Protocol (HTTPS), which employs a standard Secure Sockets Layer (SSL - 128 bit block size) encryption technology. SSL creates the secure connection, and HTTPS transmits the data securely. All subject data will eventually reside in a MySQL database server. Medication adherence data collected by using eCAP-fitted medication vials will also be collected in the study protocol. Servers hosting the REDCap database and eCAP data are maintained by the Biomedical Research Informatics Core (BRIC) at Michigan State University.

### Confidentiality {27}

The procedures for obtaining research material for the study include anthropometric and BP measurements, laboratory data (e.g., glycosylated hemoglobin {HbA1c}), medical records, interviews, and self-completed questionnaires. Research Assistants (RAs) that are trained and certified will obtain all data according to detailed study protocols. Data will be collected directly from enrolled study participants and medical records and used specifically for research purposes. Baseline data will be obtained during group visits only after the patient has signed the informed consent and the HIPAA form. Follow up data will be obtained at 0–1, 3, 6, 9, and 12 months after office visits with their providers. Only individuals officially assigned to the study team or data management team will have access to individually identifiable information about human subjects. This will include the PI, co-investigators, project coordinator, statistician, and research assistants. All individuals will have completed MSU’s IRB human subjects training and will be included on a staff listing of the MSU IRB. Patient survey information, initially collected using paper forms, will be entered into the REDCap database; EMR data will be abstracted using paper forms and later entered into the REDCap database by RAs; eCAP data will be uploaded into eCAP-Provider cloud storage by RAs and then securely downloaded by the BRIC Data Manager to a secure BRIC server.

Access to data in the REDCap database will be controlled by using user definitions and permissions, which exist within the REDCap administration module. The PI will be responsible for authorizing users and granting permissions for access to the data. Audit logs are created automatically within the REDCap application to capture the complete user history of database activity, enabling compliance to regulations of electronic records and signatures. eCAP (electronic cap for monitoring medication adherence) data will be downloaded from the eCAP provider’s cloud server by BRIC personnel and stored in de-identified format in the REDCap File Repository. The Study Statistician will access these data directly by logging in to REDCap. Daily and monthly backups of the REDCap and eCAP data will be made and retained on a server within the MSU-ITS computer data center with climate-control, motion-detection security, and swipe-card entry. REDCap variables designated as “personally identifying” will be excluded from export by using REDCap user-defined permissions. In addition, BRIC tracks the initial certification of IRB training for all REDCap users, and user access to REDCap is permitted only after documentation of certification is received.

